#### Unit of analysis and data collection

Our unit of analysis will be based on the multiple baseline assessment of individual family practice sites rather than a single group of participants being tested repeatedly before and after the introduction of the intervention. The data set at each time point will consist of patient charts, which will represent the "episode of care" used to extract outcome data for the study. To ensure the completeness and validity of the data set at each time point, we will apply the quality-control criteria of ITS designs by Ramsay *et al.*, which recommend that 80%-100% of the total number of episodes of care (*i.e.*, patient charts) be used in the data collection [27].

Once the intervention is implemented, data will be collected on all outcomes from electronic patient records (*i.e.*, PracticeSolutions^®^) and the touch-screen tablet PCs. The purpose of the pre-intervention chart review will be to establish a stable baseline of standard practice for each site. Visit-specific data (*e.g.*, initiation of osteoporosis disease management, reason for visit) will be collected bimonthly at each site by two researchers (MK and CM). To minimize the introduction of contamination that could bias results during this phase, all data collection techniques, procedures, and data collection forms will be standardized. For calibration of reliability, these two researchers will extract data from 10 randomly selected patient charts in duplicate until their agreement reaches ≥80%, at which point they will abstract data independently. The two researchers will collect data from the touch-screen tablet PCs, which will automatically generate two electronic logs each time a patient completes the RAQ. The first log will outline dated/timed RAQ responses, and the other will summarize the content of the BestPROMPT sheet. These electronic logs will be matched against patient-visit chart data to verify the use of the tool during the visit and to map any actions taken by the physician in response to the use of the RAQ.

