The objectives of the current study are to implement the osteoporosis tool prototype in three family practice settings and to conduct a pilot evaluation study to test the impact of the osteoporosis tool on disease management (*i.e.*, appropriate initiation of osteoporosis investigations and medications) using the quasi-experimental ITS design. Specifically, we will answer the following questions: (1) Does use of an osteoporosis disease-management tool by family physicians lead to enhanced osteoporosis management according to current clinical practice guidelines, as measured by increased BMD testing and prescription of osteoporosis medications such as bisphosphonates?; (2) How do clinicians perceive the utility of the tool for changing clinical practice and knowledge uptake?; (3) What is the impact of the tool on clinician adoption and satisfaction with the tool?; (4) Do family physicians use the tool in similar ways across different practice settings (*e.g.*, solo practice vs. group practice)?

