### Phase 1: implementation of the osteoporosis tool

The tool will be implemented in three family practice settings selected purposively from the Hamilton Family Health Team (FHT). This is the largest of the 150 approved primary care FHTs in Ontario, Canada, serving approximately 250,000 people [26]. It includes a comprehensive team of healthcare professionals, including 129 family physicians, 114 nurses and nurse practitioners, 20 registered dieticians, 77 mental health counsellors, 22 psychiatrists, and 7 pharmacists. A unique feature of this FHT is that all physicians use an electronic patient record system, although not every physician uses the same system [26]. We purposively selected three family practices (two solo and one group practice) that used the same electronic medical record (EMR) system (*i.e.*, PracticeSolutions^® ^[Practice Solutions, Ottawa, Ontario, Canada]) to facilitate implementation of the osteoporosis tool and subsequent data collection during the evaluation study.

To ensure optimal functioning of the prototype and to minimize disruption to usual practice, the osteoporosis tool will be tailored to the practice and workflow of each practice setting. We will complete a workflow analysis in these family practice settings to ensure the prototype's optimal functioning, minimize the disruption of the tool on usual practice, and determine if the tool could be used by patients and physicians at the point of care. Our previous work revealed that workflow differences needs to be considered during the tool design process [24,25], particularly for complex interventions that are delivered at the point of care.

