#### Sampling and population

In ITS studies, sample size calculations are related to the estimation of the number of observations or time points at which data will be collected. According to Ramsey *et al.*'s quality criteria for ITS designs, at least 10 pre- and 10 post-data points would be needed to reach at least 80% power to detect a change (if the autocorrelation is >0.4) [27]. Since the current study is a pilot, it is not known what the autocorrelation might be or what effect size the intervention is likely to produce. We therefore decided to use a relatively large number of data points to ensure that any trend or seasonal differences can be detected: 52 data points per site (where one data point = two-week segment)--26 data points before the introduction of the intervention (equivalent to 12 months' worth of two-week segments) and 26 data points after the introduction of the intervention (two-week segments for 12 months). Participants will be family physicians practicing in a solo or group practice within the Hamilton FHT and their patients at risk for osteoporosis selected according to gender- and age-eligibility criteria (*i.e.*, women ≥50 years of age, men ≥65 years of age).

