#### Analysis

Results of this ITS study will focus on the impact of the intervention on the time series, which will be tested by comparing pre- and postintervention segments of the time series to estimate the magnitude and form of the impact. "Impact" on practice will be defined according to the level of change that is observed between the baseline and postintervention periods of the study. The impact of the tool for changing practice and satisfaction with the tool will also be analyzed across the three sites. Aggregated data from each two-week segment period on primary outcomes will be analyzed using the autoregressive integrated moving average (ARIMA) approach and time-series regression models [28,29]. We hypothesize that the 26 time-point baseline assessment of practice will show no pre-intervention trend. The ARIMA approach will estimate the extent to which a significant level of change occurs between the pre-intervention and postintervention phases of the study. The multiple measurement points are necessary for the ARIMA analysis to distinguish between treatment effects and secular trends. The advantage of using the ARIMA approach for analysis is that it accounts for the three major sources of noise that may confound the analysis: trend, seasonality, and random error [28,29]. Secondary outcomes and logs of patient-initiated data from tablet PCs will be analyzed using frequency analysis of site-specific data, descriptive and inferential statistics to calculate proportions and time to completion of the RAQ (*e.g.*, means with standard deviations), and independent-sample *t*-tests or analysis of variance (ANOVA) for group comparisons (*e.g.*, differences between sites for outcomes).

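### The group practice is one site-aggregated series, so a change in physician mix near go-live can pass for a tool effect, in either direction, and no stated control adjusts for it

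*Protocol article*

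**What the plan says.** All references are to the Protocol article.

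- **Sites** (Phase 1: implementation of the osteoporosis tool): "We purposively selected three family practices (two solo and one group practice".
- **Participants** (Sampling and population): "Participants will be family physicians practicing in a solo or group practice within the Hamilton FHT", together with their at-risk patients.
- **Unit** (Unit of analysis and data collection): "Our unit of analysis will be based on the multiple baseline assessment of individual family practice sites". Patient charts make up the data at each time point.
- **Model input** (Phase 2, Analysis): "Aggregated data from each two-week segment period on primary outcomes will be analyzed using the autoregressive integrated moving average (ARIMA) approach" and time-series regression. No physician term or stratum is mentioned.
- **Effect measure** (same section): impact "on practice will be defined according to the level of change that is observed between the baseline and postintervention periods of the study". The authors expect no trend in the baseline year. They say ARIMA deals with trend, seasonality and random error.
- **Series length** (Sampling and population): "52 data points per site (where one data point = two-week segment"), split equally before and after the tool starts.
- **Threats to validity** (Phase 3 Methods; Potential limitations; Control of the implementation of the intervention; Instability): the controls are a questionnaire on professional development and practice activities, consistent recording systems and observers, a long series, and ARIMA. Physician turnover and changes in visit shares are not mentioned.

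**The concern.** Physicians decide whether to order a BMD test or prescribe, and they will not all do so at the same rate. In a solo practice with one physician, the site series is that physician's series. In the group practice it is an average weighted by each physician's share of visits, and nothing in the plan holds those shares constant over the two years. A departure, an arrival, a long leave or locum cover can therefore move the site rate while no physician changes practice.

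The stated controls do not remove this. A lasting step in provider mix is not trend, seasonality or random error. Consistent instruments concern how data are recorded, not who treats the patient. The activities questionnaire goes to participants after the intervention year. It may reveal turnover, but its answers do not adjust the series. A longer follow-up helps an initial surge to fade, but a lasting change in mix does not fade.

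At stake is the pre-post estimate in the only group practice among three sites, in a pilot meant to guide wider testing.

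**Working it through.** **1. The plan's own figure.** 52 weeks / 2 = 26 segments per year, and 26 + 26 = 52 points per site. This reproduces.

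**2. How mix enters the estimate.** The site rate is the sum of (visit share × physician rate). If no physician changes practice, the change in site rate is the sum of (change in share × rate). For two types of physician this is (shift in share) × (difference in rates). With assumed values:

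- 0.33 × (0.15 − 0.05) = 0.033, or 3.3 points
- 0.33 × (0.25 − 0.05) = 0.066, or 6.6 points
- over shifts of 10-50% and rate differences of 5-30 points: from 0.10 × 0.05 = 0.5 points to 0.50 × 0.30 = 15 points

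The sign depends on who leaves. Take four physicians with equal visits and rates of 5, 10, 10 and 15%. The site rate is 40/4 = 10.0%. It becomes 35/3 = 11.7% if the lowest leaves, and 25/3 = 8.3% if the highest leaves.

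**3. Timing and model.** One 52-point series was simulated with no tool effect and no autocorrelation: 50 or 100 visits per segment, the two rate pairs above, a 33% shift in share, 4000 runs per setting, two-sided 5%.

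| Shift in mix | Level + trends: bias | Rejects | Level only: bias | Rejects |
|---|---|---|---|---|
| None | about 0 | 4-6% | about 0 | 5% |
| Abrupt at go-live | 3.3 to 6.6 points | 26-89% | 3.3 to 6.6 points | 77-100% |
| Gradual over both years | about 0 | 5-6% | 1.7 to 3.4 points | 27-89% |
| Midway through the post year | −0.7 to −1.5 points | 5-9% | 1.6 to 3.3 points | 27-82% |

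Trend terms absorb a gradual shift. They do not absorb a step at go-live.

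**4. False-positive rate if one of k physicians is replaced at go-live.** Assumed: mean rate 10%, 50 visits per physician per segment, between-physician SD τ of 2 or 4 points, independent segments.

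- SE of level change = √(0.1 × 0.9 / (50k)) × √v
- v = 2/26 = 0.077 for level only; v = 0.308 for level plus trends over 26 + 26 points, so the SE doubles
- SD of the spurious shift = τ√2 / k
- Rate = 2 × [1 − Φ(1.96 × SE / √(SE² + shift²))]

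Example with k = 4 and τ = 4 points:

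- Shift SD = 0.04 × 1.414 / 4 = 0.01414.
- Level only: SE = 0.02121 × 0.2774 = 0.00588. The argument is 1.96 × 0.00588 / 0.01532 = 0.753, so the rate is 45%.
- Level plus trends: SE = 0.01178. The argument is 1.96 × 0.01178 / 0.01841 = 1.254, so the rate is 21%.

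| Physicians | Level only (τ = 2 to 4) | Level + trends (τ = 2 to 4) |
|---|---|---|
| 2 | 32-58% | 14-32% |
| 4 | 21-45% | 9-21% |
| 6 | 16-37% | 8-16% |

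These rates are conditional on the replacement happening at go-live. The article gives no probability for that.

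**The case against.** The strongest reply is that the site is the natural unit. The tool is installed and tailored per site, all clinic staff are trained, and two of its three components are aimed at patients. This stands: a reader might infer that site-level analysis is itself an error, and the article does not support that.

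Second, nothing in the article says that the group's physicians or their shares change. This also stands. A reader might conclude that the group-practice result will be biased, or that any change in mix shows up as a tool effect. Neither follows. The bias needs physicians with different rates. It also needs either a shift near go-live or a model without trend terms. The article names time-series regression and says trend is accounted for, so the lower range in the working may be the relevant one.

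Third, a condensed article may leave extraction fields and covariates to the full plan. This has some force, because the visit data are listed only as examples. But the article does fix the unit, the aggregation and the level-change measure, and it sets out its threats to validity with a control for each. Physician mix is not among them.

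Fourth, a reader might infer that the study question "Do family physicians use the tool in similar ways across different practice settings" cannot be answered. That goes too far. The question contrasts solo with group practice rather than physicians within the group. Tablet logs matched to visit charts, and the Phase 3 interviews, will give some information on uneven use.

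**Conclusion.** The concern holds in a limited form. For one of the three series, physician mix is an alternative explanation that the stated analysis neither measures nor adjusts for, and it can inflate or hide an effect. A step in mix near go-live is confounded with the tool under either model. A change in average mix at other times matters mainly under a level-only model.

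The 16-58% and 8-32% ranges illustrate the risk and do not predict it. The number of physicians, their rates, their visit counts and the replacement itself are all assumed. Positive autocorrelation, if modelled, would widen the standard error and lower these figures. The change is worth making because it is cheap while charts are being abstracted; later, the charts would have to be reopened.

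**What to change.** 1. Keep the site as the unit, with all visits in the primary series.
2. Add the treating physician to the standardised extraction form for every abstracted visit, in both years.
3. For the group practice, prespecify a time-series regression with physician terms (or fixed physician weights) as an adjusted or sensitivity analysis. Fixed weights need physicians who are present in both years, so the physician term is the workable form if someone is replaced.
4. Show a series restricted to physicians present in both years as a further sensitivity analysis only. If one of four equal physicians is replaced, it keeps 3/4 = 75% of visits, below the 80%-100% of episodes that the article adopts as its quality criterion.
5. Report tool use by physician within the group practice, anonymised and descriptively.

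Cost: one extra field per visit from the same electronic record, one additional model for one site, and sparser counts per physician and segment, so the adjusted estimate may be less precise.

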#### Analysis

Results of this ITS study will focus on the impact of the intervention on the time series, which will be tested by comparing pre- and postintervention segments of the time series to estimate the magnitude and form of the impact. "Impact" on practice will be defined according to the level of change that is observed between the baseline and postintervention periods of the study. The impact of the tool for changing practice and satisfaction with the tool will also be analyzed across the three sites. Aggregated data from each two-week segment period on primary outcomes will be analyzed using the autoregressive integrated moving average (ARIMA) approach and time-series regression models [28,29]. We hypothesize that the 26 time-point baseline assessment of practice will show no pre-intervention trend. The ARIMA approach will estimate the extent to which a significant level of change occurs between the pre-intervention and postintervention phases of the study. The multiple measurement points are necessary for the ARIMA analysis to distinguish between treatment effects and secular trends. The advantage of using the ARIMA approach for analysis is that it accounts for the three major sources of noise that may confound the analysis: trend, seasonality, and random error [28,29]. Secondary outcomes and logs of patient-initiated data from tablet PCs will be analyzed using frequency analysis of site-specific data, descriptive and inferential statistics to calculate proportions and time to completion of the RAQ (*e.g.*, means with standard deviations), and independent-sample *t*-tests or analysis of variance (ANOVA) for group comparisons (*e.g.*, differences between sites for outcomes).

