### Control of the implementation of the intervention

We anticipate that once the intervention is implemented, there will be an increase trend toward optimal practice according to guidelines. This sudden rise will likely occur from the implementation process rather than the intervention itself. We therefore chose a greater number of data points (which is also equal to the data points in the baseline assessment phase) to help neutralize the initial impact of the implementation and allow the true impact of the intervention to emerge.

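### Impact is worded as one level of change between two phases, which cannot show the time-varying pattern the article itself expects after go-live

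*Protocol article*

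**What the plan says.** The Analysis section of Phase 2 opens by saying that the segments before and after the intervention are compared to learn both how large the impact is and what form it takes. It then states that impact "will be defined according to the level of change that is observed between the baseline and postintervention periods of the study". For the primary outcomes it names ARIMA and time-series regression, and gives one estimated quantity: "The ARIMA approach will estimate the extent to which a significant level of change occurs between the pre-intervention and postintervention phases". Trend is listed with seasonality and random error as noise that ARIMA accounts for, and no baseline trend is expected. No term for a change in slope, a ramp or a transient is named.

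The section on control of the implementation of the intervention says: "We anticipate that once the intervention is implemented, there will be an increase trend toward optimal practice according to guidelines". The next sentence calls this rise sudden and attributes it to the implementation process, not to the tool. The remedy offered is a larger number of post-intervention points, to dilute the initial impact and "allow the true impact of the intervention to emerge".

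Sampling and population gives each site "26 data points before the introduction of the intervention" and the same number afterwards, each covering two weeks.

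**The concern.** The effect measure and the expected pattern do not fit each other. The article expects at least two things after go-live: an early rise that is not the tool, and a tool effect that becomes visible later. A single between-phase level parameter compresses both into one number. What that number means depends on how trend is handled, which the article does not say. If trend is fitted as one slope through the whole series, a gradual effect is absorbed into it. If no trend is fitted, the step is a 12-month average that mixes the early rise with whatever follows. More post-intervention points make that one number more precise but do not separate the two components. At stake is research question 1 in the Background: whether use of the tool raises BMD testing and prescribing.

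**Working it through.** **Inputs.** 26 points before and 26 after go-live per site (Sampling and population). The article gives no effect size and says the autocorrelation is unknown. Assumptions made here: AR(1) errors with correlation 0, 0.2 or 0.4 taken as known, two-sided 5% tests, effects in residual SDs, and a flat baseline (the article's own hypothesis).

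**The plan's own figures.** 26 + 26 = 52 points, and 26 × 2 weeks = 52 weeks per phase, so these agree. The statement that "at least 10 pre- and 10 post-data points would be needed to reach at least 80% power to detect a change" comes without an effect size, so it can be neither reproduced nor refuted.

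**1. Linear build-up.** Let the effect rise linearly from go-live to D at the end of segment 26, with each segment taken at its midpoint.
- Step only: post mean minus pre mean = 0.50D − 0 = 0.50D. With AR(1) 0.2 and 0.4, generalised least squares gives 0.49D and 0.47D.
- Step plus one common trend: the phases have equal length, so the fitted slope is the average of the two phase slopes, (0 + D/26)/2 = D/52 per segment. The phase centres are 26 segments apart. Step = 0.50D − 26 × D/52 = 0.00D.
- First differences: the step picks up at most one segment's increment, 1/26 = 0.04D.
- Level plus slope change: level 0.00D, slope change × 26 = 1.00D, so the ramp is recovered.

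**2. Build-up that plateaus at D (zero autocorrelation).**

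| Plateau reached at | Step only | Step + common trend |
|---|---|---|
| segment 6 | 0.89D | 0.59D |
| segment 13 | 0.75D | 0.25D |
| segment 26 | 0.50D | 0.00D |

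Counting the effect at the end of each segment gives slightly higher values, such as 0.90D and 0.66D at segment 6. For every shape, the step-only least-squares estimate equals the average effect over the 12 months.

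**3. Implementation burst with no lasting effect.** Assume exponential decay with a time constant of 3 segments. Step plus common trend returns 0.38 of the initial height as a level change (0.42 at AR(1) 0.2).

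**4. Precision cost of the slope term (zero autocorrelation).** The sum of squares of time within a phase is 26 × (26² − 1)/12 = 1462.5.
- Step only: √(2/26) = 0.277 SD.
- Step plus common trend: √(2/26 + 26²/(2 × 1462.5)) = √(0.0769 + 0.2311) = 0.555 SD.
- Level change at go-live with a slope-change term: √(2 × (1/26 + 13²/1462.5)) = √(2 × 0.1540) = 0.555 SD.
- At AR(1) 0.2 the last two are 0.647 and 0.647 to 0.648 SD.
- Month-12 difference from the projected baseline: √(2/26 + (39² + 13²)/1462.5) = √(0.0769 + 1.1556) = 1.11 SD, and about 1.33 SD at AR(1) 0.2.

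**5. Power for an effect of 1.5 SD, AR(1) 0.2.**

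| Test | Linear ramp | Pure step |
|---|---|---|
| Step only | 60% | 99% |
| Step, with common trend | 5% | 64% |
| Joint level and slope (2 df), with baseline trend | 20% | 54% |

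With no baseline trend fitted, the joint test has 74% against the ramp.

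**The case against.** A reader might infer that the plan tests only a step, strips out trend, and forecasts a gradual tool effect, so that the effect would be estimated at between zero and half its size and question 1 answered wrongly. The article does not support that.
- It also promises the form of the impact and names time-series regression, which could carry a slope term. Its phrase about a level of change can be read as an amount of change.
- It says trend is accounted for, not how. The 0.00D result belongs to one way of doing so. With no baseline trend, as hypothesised, a step alone would be a natural model and gives 0.50D.
- It calls the anticipated rise sudden and attributes it to implementation. The tool's effect emerging later is not a forecast of a steady 12-month climb.
- The zero-to-half range needs that full-year ramp and month 12 as the target. The article sets no such target, and 0.50D is the correct 12-month average.

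One could add that model terms are usually left to a fuller plan. That answers a complaint about missing detail, but here the article itself fixes what impact means and what the primary method estimates. Intending to study form does not help while no parameter carries it. If the phrase means only an amount of change, the effect measure is left open and the same clarification is needed. Reading the rise as sudden does not rescue a single level term either, because part of a fading burst is then credited to the tool.

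**Conclusion.** The mismatch stands: the declared effect measure is one between-phase change, while the article expects an effect that varies over time and needs its early part set aside. The direction and size of the error depend on shapes and trend handling that the article does not give. Under a full-year linear ramp, a level term gives from 0.00 (common trend) to about 0.50 (no trend term) of the month-12 effect. With a plateau by segment 6 it gives 0.59 to 0.89. Under a short burst with no lasting effect, a step with common trend gives a spurious 0.38 of the burst's height. All of this assumes a flat baseline, and zero autocorrelation except where stated. The point is a worthwhile correction to the analysis wording. It does not show that the study would reach the wrong answer.

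**What to change.** In the Phase 2 Analysis section, define impact as the change in level and the change in slope against the projected baseline. Add a time-since-go-live term to the time-series regression with autocorrelated errors, and report both changes with intervals. Align the section on control of the implementation with this, and state how the initial implementation rise is separated from the tool's effect. The slope term alone does not do that: with equal phases and zero autocorrelation the level estimate for a fading burst stays at 0.38, and the fade appears as a negative slope change.

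The cost is wording and one model term, with no new data. Where trend is already in the model, the standard error of the level change stays at 0.555 SD (0.647 at AR(1) 0.2). There are two downsides. A month-12 contrast is imprecise with a baseline trend in the model: at a standard error of about 1.3 SD, an effect of 1.5 SD is detected about 20% of the time. A joint 2-df test is weaker against a pure step (54%, against 64% for step plus trend and 99% for step alone), so it should be optional and not the required primary test.
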